**Figure 1 Fig1:**
[figure not shown]
**Participant flow during the study.**

#### Control group

Participants in the control group receive 5-10 min of unstructured brief smoking cessation counseling by the pharmacist (emulating current practice). In addition, they are provided with educational materials about smoking cessation and are offered nicotine replacement therapy (NRT). Before dispensing the NRT, the study pharmacist ensures that the participant does not have any contraindications to nicotine therapy and is not taking any medication that would interact with NRT. The choice of the NRT dosage form (patch or lozenge) depends on the participant’s previous experience, preference and adverse effect profile. The NRT dosage schedule and duration of therapy are similar to those in the intervention group. Control participants are not asked to attend any follow-up sessions.

The education materials address the following topics: the adverse effects of smoking, benefits of smoking cessation, the methods of quitting, setting the quit date, coping with nicotine withdrawal symptoms, getting emotional and social support, and monitoring the blood pressure and pulse when using NRT and avoiding relapse.

The study team invests a good deal of time orienting the study pharmacists on their role and training them on how to deal with the control and intervention groups. Part of that orientation is on how ‘not’ to provide any intervention to the control subset of smokers.

### Study piloting

Study pharmacists were provided with assistance in setting up the study pharmacies and given some time to familiarize themselves with the study protocol prior to commencement of the study. Then each pharmacist was asked to pilot the study in the presence of the study team. Piloting occurred by screening/recruiting around four patients in each site and by implementing the study protocol. Feedback was provided as required to the study pharmacists on the quality of patient counseling, patient education and documentation. Very minor adjustments or refinements were made to the study protocol and study tools including the patient consent form, Fagerstrom test for nicotine dependence (FTND) and smoking cessation quality-of-life (SCQOL) questionnaire as needed.

### Continuous quality improvement and evaluation plan

At all stages of the study implementation, the study pharmacists are closely supervised by the study team. Supervision is through several mechanisms including meetings, communication and site visits.

#### Meetings

Regular meetings are invaluable for high-quality supervision. Meetings are used to guide the project toward its objectives through team involvement. Bi- or triweekly meetings involving all the team members including the study pharmacists are held. In these meetings, study harmacists summarize their activities during the previous 2-3 weeks, and the study team offers them constructive feedback, acknowledges their input and suggests new directions to them. In addition, ad-hoc meetings are conducted between the study pharmacists and the study team where necessary to address any irregular issues that might arise.

#### Communication

The study team members are in direct touch with each other and with the study pharmacists through electronic communication such as emails.

#### Site visits

To maintain quality control in the smoking cessation study pharmacies, the study team visits each study pharmacy at least once every 2 to 3 weeks to monitor data collection, check protocol adherence, ensure the consistency of program delivery, address any queries that the study pharmacists might have in implementing the study, review patients’ folders for appropriate documentation, provide any on-site support required and provide individual pharmacists with feedback on their performance.

Supervision is crucial to:Orient study pharmacists to the study’s objectives and methodology and to their role in the studyMonitor and follow-up the progress of the studyTackle any issues or concerns that might arise with the study pharmacists while the study is executedShare study updatesMotivate and support the study pharmacistsEnsure adherence to the study protocol in the different study sitesEnsure standardization of study implementation in the different study sites

### Overview of utilization cost

A comparative overview of the cost of resource utilization (economic analysis) will be undertaken for the study arms in this study.

#### Model inputs and cost determination

This pharmacoeconomic analysis will be based on extrapolating data on resources from the randomized controlled trial; these data will be collected prospectively. Prospective data collection enhances the accuracy and robustness of data and limits bias.

The economic analysis is performed from a social perspective. Direct medical costs will be evaluated to the best available, including in relation to NRT, CO monitoring tests and salaries. Direct nonmedical costs will also be evaluated and will include participants’ travel costs to pharmacies (e.g., taxi) and the paperwork and forms. The indirect costs will be accounted for as well, in relation to lost productivity (if any), whether for participants or any unpaid caregivers that participants utilize. Important is that any protocol-driven costs (e.g., researchers salaries) will be excluded from the analysis.

The monetary value of resources will be collected from internal sources at the Qatari clinics. It is worth noting that costs involved in this study will be based on wholesale prices, as paid by clinics.

All calculated costs will be in Qatari Riyal, adjusted for the financial year 2015-2016, utilizing the Qatari Health Consumer Price Index as appropriate, and no discounts will be applied given the short timeframe of the analysis.

The economic evaluation will be undertaken via decision analytic modeling, where a decision tree will be structured to follow the different options and consequences in the management pathways. For each of the participants, the proposed model may include five possible treatment outcomes depending on whether participants quit smoking, and if they do, after what duration. Smokers will be initially assigned to one of two pathways depending on whether they quit smoking at enrollment. Smokers who do not quit at enrollment will be further followed until assigned to one of two pathways, depending on whether the smoker quits smoking after 3 months or not. If not, smokers will be followed up until further assigned to one of two pathways, based on whether they quit smoking after 6 months or not. Those who do not quit by then will be followed up until assigned to one of two pathways depending on whether they quit at 12 months of follow-up or not, which will be the end of follow-up in any case. Smokers who quit at enrollment or after 3, 6 or 12 months will each be followed up separately until the end of the study. Based on this, in addition to data on resources consumed and their monetary values, the model will generate a weighted average cost for patient cessation and quality-of-life adjustment. As per the general decision analysis principles, this will be calculated as the sum-product of the costs of the management outcomes and the respective probabilities.

The costs of managing the single episode of smoking cessation will be compared among different management options and against budgeted costs of clinics/government institutions.

#### Sensitivity analysis

The goal of sensitivity analysis is to indicate the robustness of the evaluation conclusion against any potential variations in the model inputs. Deterministic and probabilistic sensitivity tests will be produced by modifications on the base case values of several key variables, in relevance to costs and probabilities, to evaluate the robustness of the study economic outcome. Base case values will be substituted by the highest and lowest values within a reasonable range of values. Where a substitution changes the study economic conclusion, more values within the range will replace the base case value. This will be repeated until the exact variable value that changes the study outcome is identified. Reporting this as part of the study results not only indicates the robustness of results, but also boosts the generalizability of them when being interpreted by decision makers in other settings, with different model inputs, e.g., different resource prices.

Uncertainty analysis, by means of Monte Carlo simulation, will be performed via [contact]® analysis tool (Palisade Corp., NY, USA) to investigate the likelihood (probability) of a therapy’s economic advantage. Monte Carlo is a method whereby simulated input values, chosen randomly across a range of probability distributions of a model input, are added into the model. The model is run for each simulated input, resulting in a range of outputs characterizing the output uncertainty. Based on this, a distribution of “cost savings” will be generated, indicating the probability of one management option to have an economic advantage over another.

### Ethical considerations and confidentiality

The study protocol and all associated measures, consent forms and recruitment procedures obtained ethical approval by Qatar University (QU) and Hamad Medical Corp. (HMC) institutional review boards (QU-IRB 76/11 and HMC 11113/11). All the participants’ folders are stored in a password-protected database on the site laptop. Only the study pharmacist can access these folders. In addition, all data are retained in a password-protected database maintained along with all related study documentation in a locked cabinet at QU College of Pharmacy.

### Outcome measures

The study research assistants will call the study participants in the intervention and control groups to complete the assessment. To avoid any bias in data collection, the research assistants will be blinded to the participant group allocation.

They will measure the following outcome variables at 3, 6 and 12 months after the start of the study (i.e., the time of the participant’s enrollment in the study):Self-reported 7-day point prevalence abstinence, defined as having smoked no cigarettes for the previous 7 days at 3, 6 and 12 monthsSelf-reported 30-day point prevalence abstinence defined as having smoked no cigarettes in the last 30 days at 3, 6 and 12 monthsSelf-reported continuous abstinence defined as having smoked no cigarettes since quit day at 3, 6 and 12 monthsSmoking abstinence as objectively verified by the CO exhaled test at 12 monthsMean change in health-related quality-of-life score from baseline at 3, 6 and 12 months for quitters vs. non-quittersOverall costs of interventions as studied, including those of utilization for individual recourses consumedAverage and incremental cost-effectiveness ratio of the study smoking cessation intervention

To objectively determine long-term abstinence, at 12 months, participants who will self-report not smoking for the previous 7 days will be invited to come to their study clinic to measure their exhaled CO level. The clinic nurse who is responsible for measuring the exhaled CO level will be blinded to the study participant group. Participants will be considered abstinent if they register less than 6 ppm on the test. Interpretation of the CO test results will be made carefully taking into consideration time since last smoke, time of the day the test is done and other factors.

Exhaled carbon monoxide is a well-known indicator of cigarette smoking. But because of its short half-life (5-6 h), it only indicates very recent smoking exposure or abstinence. On the other hand, as a result of its relatively long half-life, cotinine can detect nicotine exposure for up to 1 week. However, the use of any NRT formulation can trigger a false-positive urinary cotinine test. Therefore, as it is not expensive and is noninvasive, and it gives the results in a timely manner, the exhaled carbon monoxide test is commonly used in most smoking cessation clinical trials [47].

### Data analysis

The CONSORT guidelines will be followed when analyzing the study data. Demographics and other variables related to smoking and quality of life will be summarized using frequency distributions (for categorical variables) and means with standard deviations (for numeric variables) and will be compared between the two study arms using the chi-squared test (or alternatively the Fisher’s exact test for small cell counts) for categorical variables and the independent *t*-test (or alternatively the Wilcoxon rank sum test for non-normally distributed variables) for numerical variables.

The main outcome will be continuous abstinence at 12 months as self-reported and verified by the CO test. The percentages of participants achieving the main outcome will be computed and compared between the two groups using the chi-squared test. Moreover, the difference in the proportions of continuous abstinence at 12 months between the two study arms (with 95% confidence intervals) will be computed along with the number needed to treat. Multiple logistic regression will be used to obtain the odds ratio of the main outcome between the two study arms adjusting for any imbalances in demographics or other baseline smoking-related variables. Moreover, mixed effects logistic regression, with pharmacy-level random effect, will be considered to adjust for the possible pharmacy effect if it existed. The intent-to-treat principal will be used in the analysis whereby participants who will be lost to follow-up will be classified as smokers and included in the main analysis. This includes those who were removed from the study because they could not tolerate NRT side effects. A sensitivity analysis following that of Borelli, Hogan et al. will be done where the outcome has three possible categories: abstinence, no abstinence and dropout [48]. The suggested multinomial model will allow assessing factors affecting abstinence as well as factors affecting dropout. This will aid in understanding who might need more support during the intervention. Similar analyses for the primary outcome will be done at 3 and 6 months (but do not include verification of abstinence using CO tests).

To assess the participants’ health-related quality of life, SCQOL (smoking cessation quality of life) ratings for each question will be translated into scores. A total health-related quality of life score and a domain-specific score will be calculated at baseline, 3 months, 6 months and 12 months for each participant in the intervention and control groups. The change in the total and domain-specific quality-of-life score from baseline will be calculated for each participant at 3, 6 and 12 months and analyzed using linear mixed models, which will include the quitting (quitters and non-quitters) factor and time factor (at 3, 6 and 12 months) and their interaction.

There is no interim analysis planned for this trial. Statistical analyses will be conducted using the Statistical Package of Social Sciences (IBM-SPSS®), version 21. In all analyses, the level of significance will be set at 5%.

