### Study sites

The study is implemented in eight public and private ambulatory pharmacies in the State of Qatar. These pharmacies are located within large ambulatory clinics that serve a large proportion of the Qatar population. To prevent cross contamination with the study, none of these clinics has established smoking cessation programs. Each study pharmacy is staffed by at least three pharmacists. Two pharmacists from each pharmacy are invited to participate in the study. The study is taking place in a semiprivate area in the pharmacy. This area is secluded enough to ensure adequate patient confidentiality.

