### Sample size calculation

For a priori sample size calculation, we assumed a 7-day point prevalence abstinence at 12 months of 3% for the control group and 15% for the intervention group based on the results of one of the previous studies that assessed the effect of a pharmacist-run smoking cessation program [12]. With a two-sided alpha of 5% and 90% power, a minimum sample size of 118 participants was estimated for each group. This sample size was not adjusted for the potential correlation between outcomes of patients within each clinic since this is not a clustered randomized clinical trial, but in this study patients within each clinic are randomized to the two intervention groups, and correlations, if they exist, will be very small; their effect on the power of the study is negligible [15]. The project has a total of 17 study pharmacists. Each study site is expected to enroll at least 30 participants (15 participants in the intervention group and 15 participants in the control group). The recruitment period is over 12 months (48 weeks). Recruiting at least 30 participants at each study site is considered feasible given that at least 100 patients visit each pharmacy per day. Assuming each study site will recruit 1 participant every week, the 30 needed participants will be recruited in 30 weeks (approximately 8 months). An extra 16 weeks of recruitment time is given to study pharmacists to account for workload, holidays and sickness.

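### The adjusted odds ratio is planned by multiple logistic regression with an open-ended covariate set on about 21 expected successes; a penalised fit with few covariates would remove a modest upward bias and a small risk of no estimate

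*Protocol article*

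**What the plan says.** The Data analysis section compares the main outcome, continuous abstinence at 12 months confirmed by exhaled CO, between arms with a chi-squared test. It adds the difference in proportions with a 95% interval and the number needed to treat. Then: "Multiple logistic regression will be used to obtain the odds ratio of the main outcome between the two study arms". The adjustment covers any imbalance in demographics or other baseline smoking variables, and no number of covariates is set. A mixed logistic model with a pharmacy random effect is to be considered. A three-category sensitivity analysis (abstinent, not abstinent, dropped out) follows: "The suggested multinomial model will allow assessing factors affecting abstinence as well as factors affecting dropout". Participants lost to follow-up count as smokers, so dropout adds no successes. The package named is SPSS version 21. No fitting method is named for any of these models.

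The Sample size calculation section states the expected rates: "we assumed a 7-day point prevalence abstinence at 12 months of 3% for the control group and 15% for the intervention group". It continues "With a two-sided alpha of 5% and 90% power", and "a minimum sample size of 118 participants was estimated for each group".

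**The concern.** The sample size was set to detect a difference in proportions. The adjusted odds ratio needs more from the data, and its precision and bias depend on the number of successes, above all in the sparser arm. There the plan expects three or four.

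Logistic regression fitted by maximum likelihood, the usual reading of the planned model in a standard package, is biased away from no effect when events are few. If the control arm has no success, the treatment odds ratio has no finite estimate. The adjustment rule sets no ceiling on covariates, and the initial appointment collects many candidates: sociodemographics, cigarettes per day, duration of smoking, quit attempts, family smoking, nicotine dependence and CO.

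At stake is the adjusted odds ratio. It is the only odds ratio the section names, and on average its error favours the intervention.

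**Working it through.** **Inputs.** From the Sample size calculation section: control rate 3%, intervention rate 15%, two-sided alpha 5%, power 90%, 118 per group. The number of covariates and their effects are not stated, so they are assumptions below.

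**1. The plan's own figure.** Two proportions, pooled variance, no continuity correction:

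n = [1.960 × √(2 × 0.09 × 0.91) + 1.282 × √(0.03 × 0.97 + 0.15 × 0.85)]² / 0.12² = (0.793 + 0.507)² / 0.0144 = 117.4, rounded up to 118.

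This reproduces the stated size, and power at 118 per group is 90.1%.

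**2. Expected successes.** 118 × 0.03 = 3.54 and 118 × 0.15 = 17.7, total 21.2. With eight sites of 30 (120 per arm) the total is 3.6 + 18.0 = 21.6. Per model parameter (arm plus k covariates), 21.24 / (k + 1) is 10.6 for k = 1, 4.2 for k = 4 and 1.9 for k = 10.

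**3. No control success.** (1 − p)^118 is 0.97^118 = 2.7% at the design rate. At assumed lower control rates it is 9.2% (2%), 16.8% (1.5%) and 30.5% (1%).

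**4. Crude odds ratio.** The true value is (0.15/0.85) / (0.03/0.97) = 5.71. Summing the log odds ratio over the exact binomial distributions, given that it is finite, yields a geometric mean of 6.19, or +8.5%. Most of the bias is therefore present before any adjustment.

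**5. Adjusted odds ratio.** Simulation of 5,000 trials per row, 118 per arm, true odds ratio 5.71, with a mix of continuous and binary covariates that have no effect on the outcome. Maximum-likelihood (ML) averages are over the finite fits only.

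| Covariates | ML geometric mean (excess) | ML median | No finite ML estimate | ML coverage | Firth mean log odds ratio (true 1.741) | Firth coverage |
|---|---|---|---|---|---|---|
| 1 | 6.22 (+9%) | 5.87 | 2.2% | 97% | 1.727 | 96% |
| 4 | 6.39 (+12%) | 6.10 | 3.0% | 97% | 1.740 | 96% |
| 8 | 6.73 (+18%) | 6.36 | 3.4% | 98% | 1.739 | 96% |
| 10 | 6.87 (+20%) | 6.48 | 2.7% | 98% | 1.713 | 95% |

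The Firth fit always gave a value. Its median odds ratio was 5.25 to 5.38, somewhat below 5.71: it removes the mean bias on the log scale, not every form of bias.

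**6. Sensitivity to covariate effects.** A separate simulation with truly prognostic covariates (log odds ratio 0.25 each) gave larger excesses: 7.06 against 5.99 (+18%) with 6 covariates, and 7.80 against 6.21 (+26%) with 10.

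**7. Size relative to precision.** The standard error of the crude log odds ratio at the expected counts is √(1/3.54 + 1/114.46 + 1/17.7 + 1/100.3) = 0.60. The log-scale biases in step 5 run from 1.827 − 1.741 = 0.086 to 1.927 − 1.741 = 0.186, that is 0.14 to 0.31 of a standard error.

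**8. Lower rates.** With 4 covariates of log odds ratio 0.3, 120 per arm and 2% v 10%, the finite ML fits average 5.95 against 5.44 (+9%), and 6.7% of trials have no estimate. At 1.5% v 7.5% they average 5.27 against 5.32, and 14.6% have no estimate. As successes become rarer, the main problem shifts from inflation to having no estimate.

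**The case against.** The strongest reply is that this does not touch the trial's main inference. The chi-squared test, the risk difference and the number needed to treat come first in the Data analysis section and do not depend on the logistic fit. This stands. A reader might infer that the trial's effect will be overstated or its conclusion put at risk. The document does not support that: the adjusted odds ratio is supportive, and ML interval coverage stays at 97% to 98%.

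A second reply is that few covariates may enter. If imbalance is judged by tests at 5%, 10 to 15 independent baseline variables yield 10 × 0.05 = 0.5 to 15 × 0.05 = 0.75 covariates on average. A simulation of that procedure gave 6.19 adjusted against 6.14 crude with 10 candidates, and 6.42 against 6.34 with 15, so adjustment added about 1%. This also stands as far as it goes. The excesses of 18% to 26% need 6 to 10 covariates, which the article does not imply, although nothing in it excludes them. The crude excess of about 8% remains either way.

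Third, failure to obtain a finite estimate arises mostly from an empty control cell, where the crude odds ratio fails too and the risk difference does not. That is correct, and at the design rates it concerns only about 3% of trials. The higher probabilities rest on control rates that the article does not state.

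Fourth, one might extend the criticism to the mixed and multinomial models. The first is only to be considered and the second is a sensitivity analysis. Neither is ordinary logistic regression and neither was simulated. They draw on the same successes, but no figure for their bias is offered here.

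Finally, the fitting method is not named and may be set in a fuller plan. Its absence is not the point. The article does commit to a model class, a package and an unlimited adjustment rule that suit this event count poorly, and it foresees small cells only for the baseline comparisons, where it names Fisher's exact test.

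**Conclusion.** The point holds as a modest improvement to a supportive analysis. At the design rates, maximum likelihood overstates the odds ratio by roughly 10% with few covariates and by up to about 20% with 8 to 10. It gives no finite value in about 3% of trials, or about 9% if the control rate is 2%. The bias is at most about a third of a standard error in the main simulation.

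This rests on recruitment near the stated minimum of 118 per group, on maximum likelihood as the reading of the planned model, and on assumed covariate numbers and effects. The count of about 21 is probably an upper figure, because CO-verified continuous abstinence is stricter than the 7-day point prevalence behind the 3% and 15%. How much lower the true rates would be cannot be read from the document.

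**What to change.** In the Data analysis section:

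- Fit the adjusted logistic model for the main outcome by Firth's penalised likelihood, with profile-likelihood intervals.
- Limit the adjustment to a few covariates, instead of any variable found imbalanced.
- If the multinomial sensitivity model is reported, use a bias-reduced fit for it too.
- Keep the risk difference with its 95% interval, already planned, as the headline estimate.

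The cost is a few sentences, with no change to design, sample size or data collection. The small downside is that these models may have to be run outside SPSS 21 or with an add-on.

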### Initial appointment and randomization

One to two days before his or her scheduled appointment, the study pharmacist contacts the enrolled participant to remind him or her about the appointment. At this initial appointment, which takes around 30 min, the study pharmacist first collects the participant’s sociodemographic characteristics, current medical problems and medications, smoking history (i.e., number of cigarettes per day, duration of smoking, previous quit attempts, smoking habits of other family members and the participant’s reasons for wanting to quit smoking) and vital signs (i.e., blood pressure and pulse). In addition, the pharmacist assesses the smoker’s level of nicotine dependence using the Fagerstrom Test for Nicotine Dependence and measures his or her baseline exhaled carbon monoxide (CO) level using the exhaled CO test. Furthermore, the pharmacist administers the smoking cessation quality-of-life (SCQOL) questionnaires. After baseline data collection, the smoker is randomly assigned to either the intervention group or the control group. Randomization is already anonymously preset by the study statistician for each study pharmacist. According to the participant number and the preset list, the participant will be randomized to the intervention or control group. A new appointment is set with the participants assigned to the intervention group. Participants assigned to the control group receive brief unstructured smoking cessation advice as outlined below. Participants in both groups do not pay for their participation.

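### The adjusted odds ratio for the main outcome takes its covariates from chance baseline imbalances instead of a short list named in advance

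*Protocol article*

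**What the plan says.** The Data analysis section of the protocol article defines the outcome: "The main outcome will be continuous abstinence at 12 months as self-reported and verified by the CO test". The first comparison is unadjusted: "The percentages of participants achieving the main outcome will be computed and compared between the two groups using the chi-squared test". A difference in proportions with a 95% confidence interval and a number needed to treat follow.

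A multiple logistic regression then gives an odds ratio between the arms, "adjusting for any imbalances in demographics or other baseline smoking-related variables". No covariate is listed and imbalance is not defined. Earlier in the section, baseline variables "will be compared between the two study arms using the chi-squared test" or its counterparts for small counts and numeric variables, and a 5% level is set for all analyses. The text does not say that these baseline tests decide what counts as imbalanced. A pharmacy random effect "will be considered to adjust for the possible pharmacy effect if it existed".

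Under Initial appointment and randomization, the pharmacist records the smoking history ("number of cigarettes per day, duration of smoking, previous quit attempts, smoking habits of other family members"), administers the Fagerstrom test and "measures his or her baseline exhaled carbon monoxide (CO) level using the exhaled CO test". All of this precedes allocation, which follows a preset list for each pharmacist.

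**The concern.** With individual randomisation from a preset list, a baseline difference between arms is a chance event. How large it is says nothing about whether the variable predicts quitting. A rule that admits covariates because they look imbalanced therefore selects on the wrong property: it can bring in a variable unrelated to quitting and leave out one that is strongly related but happens to be balanced.

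Two things are at stake.

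- **Meaning of the estimate.** The odds ratio is non-collapsible, so its target value depends on which predictors are in the model. Under this rule nobody can say in advance what the adjusted odds ratio estimates, and an undefined imbalance leaves the analyst free to choose.
- **Use of the data.** Whatever precision the baseline smoking variables offer is usually forgone, although they are collected on everyone.

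The Data analysis section also plans similar analyses at 3 and 6 months, so the rule is likely to carry over to them.

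**Working it through.** **1. The plan's sample size.** Inputs from Sample size calculation: 3% v 15%, two-sided alpha 5%, power 90%, 1:1.

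n = [1.960 × √(2 × 0.09 × 0.91) + 1.282 × √(0.03 × 0.97 + 0.15 × 0.85)]² / 0.12² = (0.793 + 0.507)² / 0.0144 = 117.4, so 118 per group. The stated figure is reproduced. Naming covariates does not alter it.

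**2. Events available.** 118 × 0.03 + 118 × 0.15 = 3.5 + 17.7 = 21.2. The planning rates are for 7-day point prevalence. The main outcome is CO-verified continuous abstinence, which is stricter, so 21 is probably optimistic. If both rates were halved (an assumption) there would be 10.6. Either way the model can carry only a few covariates.

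**3. How often a given predictor is left out.** Under randomisation a variable tested at level α is flagged with probability α. The plan gives no criterion, so a range is shown.

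| Assumed criterion | One given predictor left out | At least one of 10 independent variables flagged |
|---|---|---|
| p < 0.05 | 95% | 1 − 0.95^10 = 40% |
| p < 0.10 | 90% | 1 − 0.90^10 = 65% |
| p < 0.20 | 80% | 1 − 0.80^10 = 89% |

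An informal rule such as a standardised difference above 0.1 gives: SE = √(2/118) = 0.130; 0.1/0.130 = 0.77; flagged 44%, left out 56%. The count of 10 and the independence are assumptions; smoking measures are likely to be correlated. Under each of these criteria, inclusion is decided by chance and a given predictor is left out more often than not.

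**4. Consequences by simulation.** Assumptions not in the documents: 10 independent baseline variables, 2 of them predictive, selection at p < 0.05, 118 per arm, 1,500 trials per scenario. Power is at 3% v 15%; type I error is at 9% in both arms.

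| Log OR per SD of each predictor | Quantity | Unadjusted | Imbalance-selected | Two named in advance |
|---|---|---|---|---|
| 0.5 | Power | 90.7% | 90.5% | 91.3% |
| 0.5 | Type I error | 5.7% | 5.5% | 5.9% |
| 0.8 | Power | 91.3% | 91.2% | 93.1% |
| 0.8 | Type I error | 3.9% | 3.5% | 3.3% |

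The gain from naming covariates is 91.3 − 90.5 = 0.8 and 93.1 − 91.2 = 1.9 points. The simulation standard error is about 0.8 points for each power and 0.6 for each type I error. In the two power scenarios, 34 and 37 of the 1,500 trials were dropped because the fit failed or a treatment log odds ratio exceeded 6 in size, which itself shows how sparse the control events are.

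A given predictor was selected in 4.9% to 6.6% of trials. Between 59 and 69 different covariate sets arose per scenario, and about 60% of trials had no covariate.

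**5. Shift in meaning.** The unadjusted log odds ratio for 3% v 15% is ln(0.15/0.85) − ln(0.03/0.97) = 1.74 (odds ratio 5.7). With two predictors at 0.8 per SD, the conditional value that produces the same two rates is 1.92 (odds ratio 6.9). The mean estimates were 1.81 with imbalance selection and 2.02 with the two named; both run somewhat above their targets with so few events.

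**6. Pharmacist terms.** Sample size calculation gives 17 pharmacists. Indicators would need 17 − 1 = 16 parameters against about 21 events.

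**The case against.** The strongest reply is that this is a supporting estimate. The comparison named first is an unadjusted chi-squared test, followed by a risk difference and number needed to treat, and none of them uses covariates. That stands. A reader might infer that the trial's main inference is at the mercy of chance imbalances; the text does not support this.

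A reader might also infer that baseline p-values below 0.05 decide the model. The article places the baseline tests and the imbalance wording in the same section but never links them, so every selection frequency above is conditional on an assumed criterion. Nor does it give a number of baseline variables.

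Inflated false-positive risk or a misleading confidence interval is a third tempting reading. Type I error under the imbalance rule was 3.5% and 5.5%, close to nominal, and interval coverage was not computed, so neither is claimed.

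The planned multinomial sensitivity analysis can examine factors related to abstinence whatever their balance, so the baseline variables are not wholly ignored. The article also does not itself show which of them predict quitting. Both points stand, but neither fixes the covariates of the adjusted odds ratio.

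Finally, a separate analysis plan may name covariates. It would then have to replace a rule stated here, not fill a gap.

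**Conclusion.** The point holds for the adjusted odds ratio of the main outcome, and only there. Its covariates, and therefore its target value, are fixed by chance after the data are seen, and baseline smoking variables measured on everyone are usually left out: about 95% of the time for any one of them at an assumed 5% criterion, and 56% even under a loose standardised-difference rule.

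The measurable cost is small: roughly 0 to 2 points of power under assumed predictor strengths, no clear type I error inflation, and no change to the 118 per group. The case for changing the text rests mainly on giving the estimate a fixed meaning and removing analyst choice. It does not rest on a threat to the trial's validity.

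**What to change.** In Data analysis, replace the imbalance wording with a short list named now and included whatever the observed balance. Fagerstrom score and cigarettes per day (or baseline CO) would be a reasonable pair; the investigators should settle the choice on prognostic grounds. Keep it to about two, given some 21 expected events and possibly fewer. State that baseline significance tests will not be used to choose covariates.

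If pharmacist or pharmacy enters the model, use a random effect or a stratified analysis, not 16 indicator terms. A sparse-data method such as Firth's penalised likelihood and a covariate-adjusted risk difference are optional additions.

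The cost is a small change of analysis wording. The variables are already collected, and the article reports recruitment as ongoing, so the change could be made before outcomes are analysed. The downside is less freedom to adjust for an unexpected imbalance; that adjustment can be reported as a labelled sensitivity analysis.
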